#### Secondary Outcomes

##### Overview

To comprehensively evaluate postoperative recovery and investigate potential mechanisms, the subsequently mentioned secondary outcomes will be monitored. The first outcome is the incidence of PONV. The frequency of PONV episodes will be recorded every 4 hours. The second outcome is postoperative inflammatory markers. To establish baseline values and track the perioperative inflammatory trajectory, venous blood samples for quantification of WBC count and serum amylase levels will be collected before surgery, at 3 hours after surgery, and on the morning of postoperative day 1. These parameters will serve to assess pancreatic functional recovery, screen for complications, and gauge the magnitude of the systemic inflammatory response. Furthermore, they will provide indirect indicators of gastrointestinal functional status, offering valuable reference data for monitoring postoperative clinical progression.

##### Adherence

To ensure strict adherence to the intervention plan, researchers will actively communicate with both the parents and the child to confirm the timing of the intervention, thereby ensuring that participants can attend on time. Additionally, the child will receive a gift upon enrollment and again at the conclusion of the final follow-up to enhance motivation and engagement throughout the study.

##### Data Collection and Management

Data collection will be conducted by trained, blinded researchers. Baseline data will be collected after the children have completed random allocation and before the initiation of the first intervention. Data will be meticulously recorded during each acupoint massage session and the application of mirabilite, which includes specific time points of the intervention, actual duration of execution, selected acupoints for acupressure, intensity of techniques, site of mirabilite application, and the child’s tolerance and compliance with the intervention. Core observational indicators for postoperative recovery will be collected strictly, with the times of first flatus and first bowel movement recorded through scheduled inquiries by medical staff to the child or family, validated through physical examinations, and accurately documented. Instances of PONV will also be recorded, while inflammatory indicators will be documented at 3 hours after surgery and the following morning.

All collected data will be recorded using standardized paper CRFs. All paper CRFs will be securely stored by the principal investigator, and data entry will follow a double-entry system. An electronic database will be established using Microsoft Excel, with regular checks to identify potential errors or outliers. Source data verification will be performed regularly, comparing CRF data with original medical records to ensure transcription accuracy.

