### Randomization and Blinding

This study uses a randomized block design with a block length of 4. Random numbers for grouping were generated using Stata (version 18.0; StataCorp). A dedicated researcher, who will not participate in the recruitment of participants or data collection, will oversee the random grouping process, thereby ensuring that the grouping decisions remain independent of actual operations. Before the initiation of the study, personnel not involved in participant recruitment or data collection will create an allocation table based on the random number sequence and maintain this table in strict confidentiality to prevent any potential leaks. Group allocations will be concealed within sealed, opaque envelopes, which the researcher will open before the intervention to access the allocation plan for each patient.

Given the overt nature of acupoint massage and external mirabilite application, blinding of participants, their guardians, and the health care providers administering the interventions was not feasible. This represents an inherent methodological limitation of this study. To mitigate potential measurement bias due to the lack of blinding, we implemented several procedural strategies. A strict and standardized outcome assessment protocol was established, wherein independent assessors, specifically nurses who were blinded to group allocation, evaluated patients at 4-hour intervals. These evaluations were conducted through direct auscultation of bowel sounds combined with patient or parental reporting. Documentation of first flatus or defecation requires both active bowel sounds and clear verbal confirmation, thereby reducing sole reliance on subjective reporting. Researchers responsible for data collection and statistical analysis remained blinded to group assignment and accessed only deidentified datasets to maintain analytic independence. Furthermore, throughout the informed consent process and study duration, families received standardized, neutral communication, emphasizing that the study aimed to compare different postoperative care approaches, avoiding implications of differential efficacy to reduce expectation bias. All outcomes were recorded on structured case report forms (CRFs), mandating concurrent documentation of objective signs, such as auscultation findings, alongside the reporting source.

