##### Quality Control and Precautions

The research team developed a comprehensive standard operating procedure in advance, clearly delineating the intervention specifics related to acupoint massage and the external application of mirabilite. Before the formal commencement of the study, all intervention researchers must undergo unified theoretical and practical training, focusing on controlling the intensity of the technique and accurately locating acupoints. Consistency assessments will ensure a high degree of homogeneity and reproducibility in intervention measures among different practitioners.

Safety monitoring will be conducted continuously throughout the intervention process. During each acupoint massage session, the operator must assess and document the child’s tolerance to the treatment in real time, with particular attention to controlling the acupressure intensity to minimize discomfort or injury. Before, during, and after each application of mirabilite, skin reactions in the treated area must be closely monitored and documented, emphasizing any allergic or irritative symptoms, such as rashes, itching, blisters, or ulceration, as well as the child’s reported discomfort. Any adverse events or suspected adverse reactions, irrespective of their relation to the research intervention, must be recorded promptly and thoroughly according to the protocol, detailing the time of occurrence, manifestations, severity, duration, management measures, and outcomes.

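### Data collection is assigned without exception to blinded researchers, yet it includes session records that reveal the arm, and de-identification does not hide allocation

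*Protocol article*

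**What the plan says.** Under Data Collection and Management, the protocol article opens with "Data collection will be conducted by trained, blinded researchers" and excepts no category of data. Two sentences later it says "Data will be meticulously recorded during each acupoint massage session and the application of mirabilite", and the items named include "selected acupoints for acupressure, intensity of techniques, site of mirabilite application", along with session timing, actual duration, tolerance and compliance. The next paragraph adds "All collected data will be recorded using standardized paper CRFs" and "An electronic database will be established using Microsoft Excel", with double entry and source verification.

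Under Randomization and Blinding, the article states: "Researchers responsible for data collection and statistical analysis remained blinded to group assignment and accessed only deidentified datasets". Ethical Considerations explains that identity is replaced by a study number, with the linkage file kept apart.

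Two other roles are described. Randomization and Blinding gives the 4-hourly checks for flatus and defecation to separate nurses masked to allocation. Quality Control and Precautions says that, at each massage session, "the operator must assess and document" the child's tolerance.

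**The concern.** The people who deliver treatment, the children and the guardians all know the allocation, as the article accepts. The single-blind label therefore rests on the outcome assessors, the data collectors and the analysts. For the collectors, the written procedure contradicts the claim, because nobody can note which acupoints were pressed, or where the paste was placed, and remain unaware of the arm. De-identification does not repair this, since it acts on identity and not on allocation.

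What is at stake is judgement exercised after the event. Both primary times depend in part on what the child or family reports, so entries may be queried or corrected during cleaning. The Data Analysis section also leaves choices to the data: covariates enter the Cox model on a univariable P value below .10, and for continuous variables the parametric or nonparametric test follows the observed distribution. These decisions are safer when made without sight of the arm.

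**Working it through.** The plan gives no figure on this point, so the check compares sections and then asks whether the recorded items identify the arm.

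**Step 1. Can the blinding statement and the session record both stand?** The first sentence of Data Collection and Management covers all data collection. The session items appear in the same paragraph as part of that collection. There are two readings:
- The blinded researchers record the sessions. They are then not blind.
- The operators record the sessions, as Quality Control and Precautions says for massage tolerance. The opening sentence is then too broad, because part of the data is collected by unblinded staff.

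Either way the opening sentence needs correcting. The second reading removes the tension between the two sections but leaves that sentence wrong.

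**Step 2. Do the items identify the arm?** The conventional care group receives neither intervention, and the combination group receives both. The possible patterns number 2 × 2 = 4:

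| Massage items | Mirabilite items | Arm |
|---|---|---|
| present | absent | acupoint massage |
| absent | present | mirabilite |
| present | present | combination |
| absent | absent | conventional care |

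The match is one to one. Anyone who fills in, enters, verifies or analyses a full record can read the arm without an allocation code. The upper bound is all 72 planned children.

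**Step 3. Does a stated safeguard break the link?** De-identification replaces identity with a study number and leaves all four patterns intact. The intervention table asks for separate documentation in the combination group, but that separates massage from mirabilite, not treatment from outcome. The article states no split between session and outcome records, and no removal of session items before analysis.

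**Step 4. How far does this reach?** For collectors it follows directly from the text. For analysts it is conditional: one database is described for the collected data, but the contents of the analysis file are not stated. For the 4-hourly assessors it does not follow, because they are a separate role and nothing says they see session records.

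**Step 5. How many children can a change of forms still protect?** As of January 2026, 38 of 72 had been randomized, leaving 72 − 38 = 34. A masked analysis file can still serve all 72.

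**The case against.** The strongest defence is that the session sentence is passive and names no recorder. Read with Quality Control and Precautions, it may mean that operators record sessions while blinded staff collect outcomes. The forms are plural and not shown, and their layout and the contents of the analysis extract would usually sit in a fuller document. The analyses described name no session-delivery variable, so the analyst has no need of those items. The article also asserts blinding to assignment as well as de-identification. These points stand to this extent: they make a benign practice plausible, and missing detail on forms or extracts is not itself a fault in an article. They do not rescue the unqualified opening sentence, which is contradicted within its own paragraph.

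A reader might infer more than the text supports:
- That one person holds both the session record and the outcome inquiry, so that the primary outcomes are assessed unblinded. No section says so, and the independent masked nurses point the other way.
- That the primary times rest only on asking the family. The article also requires auscultation, and documentation of objective signs together with the reporting source.
- That the analysts' file certainly reveals the arm. The article does not say what that file contains.
- That covariate choice is open to free discretion. A stated P-value rule limits it.

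**Conclusion.** The concern holds in a limited form. The article claims blinding for everyone who collects data, and its own list of session items shows that this cannot be true of whoever records or enters them. De-identification masks identity, not allocation, so analyst blinding also fails if session items are in the analysis file; that is a condition, not an established fact. The bound of 72 of 72 children applies only to a person who sees the full record. It assumes that massage and mirabilite items are filled in only where that treatment was given. No bias in flatus or defecation times can be computed from the document, and the outcome assessors are not shown to be unblinded. The point deserves correction because the blinding claim will be relied on when the results are read, and the remedy is cheap while recruitment continues.

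**What to change.** 1. In Data Collection and Management, limit the blinding statement to outcome and laboratory data and name the operators as recorders of session data. Reconcile this with Randomization and Blinding and with Quality Control and Precautions.
2. For children still to be enrolled (34 as of January 2026), split the case report form. The operators, already unblinded, complete a session and safety form covering delivery, tolerance and skin checks. The blinded nurses complete an outcome form with no intervention items and have no access to the session form.
3. For all 72 children, give the analyst an outcome file with neutral arm codes and no session, tolerance or skin items. Reveal which code is routine care only after data cleaning and covariate choices are locked. That step is needed because the three primary contrasts are each against routine care. The combination code is then needed for the exploratory contrasts, if they are reached. Release session and safety data after the primary analysis.
4. In the final report, state that blinding of data collectors may not have held for children already enrolled if those collectors recorded session data.

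The cost is a reformatted form and a data-release step. Operators already document massage tolerance, so the added recording should be small, but the article does not establish who completes the remaining session items and the sponsor should confirm this.

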##### Quality Control and Precautions

The research team developed a comprehensive standard operating procedure in advance, clearly delineating the intervention specifics related to acupoint massage and the external application of mirabilite. Before the formal commencement of the study, all intervention researchers must undergo unified theoretical and practical training, focusing on controlling the intensity of the technique and accurately locating acupoints. Consistency assessments will ensure a high degree of homogeneity and reproducibility in intervention measures among different practitioners.

Safety monitoring will be conducted continuously throughout the intervention process. During each acupoint massage session, the operator must assess and document the child’s tolerance to the treatment in real time, with particular attention to controlling the acupressure intensity to minimize discomfort or injury. Before, during, and after each application of mirabilite, skin reactions in the treated area must be closely monitored and documented, emphasizing any allergic or irritative symptoms, such as rashes, itching, blisters, or ulceration, as well as the child’s reported discomfort. Any adverse events or suspected adverse reactions, irrespective of their relation to the research intervention, must be recorded promptly and thoroughly according to the protocol, detailing the time of occurrence, manifestations, severity, duration, management measures, and outcomes.

Emergency response plans have been pre-established to address potential safety issues. To manage possible skin allergic reactions resulting from the external application of mirabilite, emergency medications will be readily available on-site for localized treatment; should a clear allergic reaction or severe skin irritation arise, the application of mirabilite will be immediately terminated, symptomatic treatment will be administered, and adverse events will be reported as required. If a child shows discomfort, distress, or verbal or behavioral refusal during an intervention, the procedure will be paused immediately. The researcher will comfort the child and consult with the guardian. The intervention may resume only if the distress is transient and the child and guardian agree. Continued refusal or significant distress will lead to termination of that session or withdrawal from the study. All research personnel must be thoroughly familiar with and strictly adhere to these safety protocols and emergency plans, prioritizing the safety of the children involved and promptly reporting any incidents that exceed the prescribed protocols or severe adverse events to the principal investigator and the ethics committee.

### Data Analysis

Statistical analyses will be performed using SPSS (version 25.0; IBM Corp) and RStudio (Posit PBC), incorporating the *survival* package. A 2-sided significance level of .05 will be applied for all tests, and an intention-to-treat analysis will be implemented to handle missing data.

Categorical baseline variables will be summarized as frequencies and percentages, with group comparisons conducted using chi-square tests or Fisher exact tests as appropriate. Continuous variables will be described as mean with SD if normally distributed and compared via 1-way ANOVA; nonnormally distributed variables will be presented as median with IQR and compared using the Kruskal-Wallis *H* test. Time-to-event analysis will be applied to the primary outcomes, namely time to first flatus and time to first defecation. Cumulative event rates will be visualized using Kaplan-Meier curves, and overall, between-group differences will be assessed via the log-rank test. To address multiple comparisons, a prespecified hierarchical contrast approach will be used. Primary contrasts, including each intervention group compared to the routine care group, will be evaluated using a Bonferroni-adjusted significance threshold of .0167. Exploratory pairwise contrasts between the combination group and each monotherapy group will be conducted only if significant differences are observed in the primary contrasts. Additionally, a Cox proportional hazards regression model will be used to estimate adjusted hazard ratios with 95% CIs for each intervention relative to routine care while controlling for baseline covariates identified in univariable analysis with a *P* value of <.10.

The secondary outcome analysis will include comparisons of PONV incidence using chi-square tests, with Bonferroni-adjusted pairwise testing where applicable. Inflammatory markers, including WBC count and serum amylase, will be analyzed using repeated-measures ANOVA to evaluate changes at 3 hours after surgery and on the morning of postoperative day 1. Safety outcomes will be summarized descriptively, and between-group differences in adverse events will be examined using chi-square or Fisher exact tests.

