### Sample Size

G*Power (version 3.1; Heinrich Heine University Düsseldorf) software was used to calculate the sample size. We used the *F* test as the method for statistical analysis, establishing an α of .05 and a power (1–β) of .95. The estimation was based on data from a previous high-quality clinical trial, which used a 3-arm parallel design evaluating combined mirabilite application with massage, massage alone, and mirabilite application alone in patients undergoing laparoscopic hepatectomy [23]. Using the reported group means, a pooled SD of 13.03 hours, and a sample size of 30 per group from that trial, the software estimated an effect size (*f*) of 0.593. On the basis of this effect size, the calculated total sample size required for this 4-group study was 56 participants. To account for an anticipated dropout rate of 20%, the final planned total sample size is 72 participants, with approximately 18 (25%) individuals allocated to each group.

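### Intention-to-treat is named as the way to handle missing data, which it cannot do; the PONV chi-square is left with no workable rule for children who leave without a recorded episode

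*Protocol article*

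**What the plan says.** In the protocol article, Data Analysis gives one sentence on missing data: "an intention-to-treat analysis will be implemented to handle missing data". It names no imputation, model-based method or sensitivity analysis beside it.

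Sample Size expects losses: "To account for an anticipated dropout rate of 20" per cent, 56 children are raised to 72, about 18 per group.

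The primary outcomes, time to first flatus and time to first defecation, are analysed by Kaplan-Meier, log-rank and Cox methods. The secondary analysis consists of "comparisons of PONV incidence using chi-square tests", with repeated-measures ANOVA for WBC count and serum amylase. PONV is recorded every 4 hours (Secondary Outcomes).

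Children can leave by voluntary withdrawal, by loss of contact that prevents further assessment, or after a serious adverse event (Participants). During an intervention there is a further route: "Continued refusal or significant distress will lead to termination of that session or withdrawal from the study" (Quality Control and Precautions).

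**The concern.** The sentence gives intention-to-treat a task it cannot perform. The principle says that every randomised child is analysed in the allocated group. It does not say what value to use when the outcome is unknown.

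This is more than an omitted detail that an unseen analysis plan might supply. A method is named, it is the wrong kind of method, and an analysis plan that followed the sentence would inherit the fault.

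It matters most for PONV. A child who leaves loses all later 4-hourly checks, and the chi-square has no way to use a child observed for part of the period. At stake are the PONV incidence in every arm and, if leaving differs between arms or depends on PONV, the comparison between arms.

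**Working it through.** **1. The plan's own figures.** Inputs from Sample Size: "the software estimated an effect size (*f*) of 0.593", four groups, "establishing an α of .05 and a power (1–β) of .95". One-way ANOVA F test, noncentrality N × f², degrees of freedom 3 and N − 4:
- N = 52: power 0.946. N = 56: power 0.962. The smallest N is 53, or 56 with equal groups, so 56 reproduces.
- 56 / (1 − 0.20) = 70, or 72 as the next multiple of 4, so 72 reproduces.
- 0.20 × 72 = 14.4, so about 14 children are expected to leave (3 to 4 per arm) and about 58 to remain.

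The sample size is not at fault. It plans for about 56 children with data, while intention-to-treat covers all 72. The sentence on missing data has to bridge that gap.

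**2. What each named analysis can do with a child who leaves.**
- Log-rank and Cox, primary outcomes: censor at the last check. No gap.
- Chi-square on PONV, episode already recorded: a known yes. No gap.
- Chi-square on PONV, no episode recorded: no value. The child enters as PONV-free or is left out.
- Repeated-measures ANOVA in its usual form: a child lacking one of the blood samples drops out.

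**3. Incidence if leavers without an episode are counted as PONV-free.** The documents give no PONV rate, observation window or timing of withdrawal. Assumed: incidence p of 30 to 50% over 24 h at a constant hazard h = −ln(1 − p)/24, and 20% leaving uniformly over the first T = 12 or 24 h, unrelated to PONV. The chance that a leaver has an episode on record is r = 1 − (1 − exp(−hT))/(hT). Incidence is too low by 0.20 × (p − r).
- p = 0.30, T = 24: hT = 0.357, r = 0.159; 0.20 × 0.141 = 2.8 points.
- p = 0.50, T = 12: hT = 0.347, r = 0.155; 0.20 × 0.345 = 6.9 points.

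The range is about 3 to 7 points.

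**4. Difference between arms under the same rule.** With d1 leaving in an active arm and d0 in control, and no true effect, the bias is −(d1 − d0) × (p − r).
- 20% v 20%: zero.
- 25% v 5%: −2.8 to −6.9 points.
- All dropout in the three active arms, 0.20 × 4/3 = 26.7% v 0%: −3.8 to −9.2 points. With SE = sqrt(2p(1 − p)/18), which is 15.3 points at p = 0.30 and 16.7 at p = 0.50, that is 0.25 to 0.55 SE.

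**5. Dropping leavers does not protect if leaving is related to PONV.** Assumed: true PONV 40%; 35% of children with PONV and 10% of the others leave before anything is recorded. Total leaving is 0.40 × 0.35 + 0.60 × 0.10 = 20%. Dropped: 0.40 × 0.65 / 0.80 = 32.5%. Counted as PONV-free: 0.40 × 0.65 = 26%.

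**6. Illustration at 18 per arm, four leavers in each.** Suppose 8/14 v 3/14 are observed (uncorrected chi-square).
- Leavers dropped: p = 0.053.
- All PONV-free (8/18 v 3/18): p = 0.070.
- All with PONV (12/18 v 7/18): p = 0.095.
- Opposite directions by arm: p = 0.002 (12/18 v 3/18) to 0.74 (8/18 v 7/18).

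**The case against.** The strongest reply is that the article nowhere says leavers are counted as PONV-free or dropped. A chi-square can be run on imputed data, and the analysis plan, which is not shown, may say so. It is right that neither classification is stated. Both are inferences from the methods the article names, and the point is put in that form. The reply does not rescue the sentence, which assigns the task to a principle that cannot do it.

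A reader might also infer that only the active arms can lose children through refusal, so that the bias favours the interventions. The documents do not support that:
- The withdrawal reasons under Participants apply to all arms, and Ethical Considerations lets any child withdraw assent at any time.
- Conventional-care children also undergo 4-hourly questioning and auscultation and blood sampling, which they may refuse.
- Only refusal of massage or mirabilite is confined to the active arms, and ending the session is offered there as an alternative to withdrawal.

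Further limits stand. The 20% is a planning allowance for what appears to be a short inpatient stay, and actual loss may be smaller. Children with an episode before leaving are known cases; Table 2 lists a stop for vomiting during massage, so some active-arm stops may coincide with recorded events. The wide range of p-values in the illustration is what any binary outcome would show with 4 of 18 missing per arm.

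**Conclusion.** The point holds in a limited form. The missing-data sentence is wrong as written, and PONV is where it bites, because the chi-square cannot use a child observed for part of the period.

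If leavers are counted as PONV-free, incidence is about 3 to 7 points too low. This rests on an assumed true incidence of 30 to 50%, an assumed 24-hour window and the planned 20% loss. Equal loss unrelated to PONV gives no bias between arms. Unequal or outcome-related loss is possible, but its direction and size are not established. In particular, the figure of about 4 to 9 points requires all dropout to fall in the active arms, which nothing in the documents shows.

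The primary outcomes and the sample size are not affected.

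**What to change.** Replace the sentence with the following:
- All randomised children are analysed in their allocated group; intention-to-treat is the analysis set.
- PONV incidence is estimated by Kaplan-Meier on time to first recorded episode, read at a stated time after ERCP. A withdrawn child is censored at the last 4-hourly check, and groups are compared by log-rank.
- Sensitivity analyses count withdrawn children without an episode as all having PONV, as none having PONV, and in opposite directions by arm.
- WBC count and amylase are analysed by a mixed model for repeated measures, which keeps children with partial data, in place of complete-case repeated-measures ANOVA.

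The cost is analysis wording and a few extra runs. No new data are needed: the 4-hourly records give the times, and survival software is already named. With 38 of 72 children enrolled as of January 2026 and no interim analysis done, the change can be made before outcomes are analysed. The downside is that the main estimates assume withdrawal is unrelated to later outcome. The sensitivity analyses test this for PONV only; for WBC and amylase it remains an assumption.

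### The three primary contrasts are tested at a flat Bonferroni .0167; Holm over the same stated family would keep the .05 bound and gain power (an efficiency gain, not an error)

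*Protocol article*

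**What the plan says.** The Data Analysis section sets a general level: "A 2-sided significance level of .05 will be applied for all tests". For multiplicity it states that "a prespecified hierarchical contrast approach will be used" and then describes two tiers.

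- **First tier:** "Primary contrasts, including each intervention group compared to the routine care group" "will be evaluated using a Bonferroni-adjusted significance threshold of .0167". The threshold is the same for all three contrasts, and no ordering or step-down among them is described.
- **Second tier:** the exploratory comparisons of the combination with each monotherapy "will be conducted only if significant differences are observed in the primary contrasts".

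The analysis covers two endpoints: "Time-to-event analysis will be applied to the primary outcomes, namely time to first flatus and time to first defecation". No division of alpha between them is given.

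The Sample Size section rests on an omnibus F test, "establishing an α of .05 and a power (1–β) of .95", and "the software estimated an effect size (*f*) of 0.593". It gives no power for a pairwise contrast at .0167.

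**The concern.** A single-step Bonferroni rule holds each contrast to .0167 however strong the other two are. Holm relaxes the threshold as contrasts are rejected, needs no extra assumption, and keeps the same familywise bound. For the reject-or-not decision, Bonferroni therefore never does better than Holm.

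This matters more here than in many trials. The Introduction hypothesises that all three strategies beat routine care, and Study Aims makes all three comparisons primary. A trial that hopes to reject several hypotheses is where step-down testing pays. The monotherapy contrasts, at about 18 children per arm, lose most from the flat threshold.

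**Working it through.** **Inputs from the protocol.** Two-sided alpha .05; three primary contrasts; threshold .0167; 1:1:1:1 allocation; f = 0.593; SD 13.03 h; 56 evaluable children (14 per arm); 72 planned (18 per arm).

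**The plan's own figures.**
- Threshold: .05/3 = .016667, which is .0167 as stated.
- Sample size: one-way ANOVA, k = 4, noncentrality N × f². Power first reaches .950 at N = 53. Rounding up to equal arms gives 56, with power .962. Stated 56 is reproduced.
- Dropout: 56/0.8 = 70, or 72 as four equal arms. Stated 72 is reproduced.

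**The two rules.** Bonferroni rejects every p ≤ .05/3. Holm orders the p-values and compares them with .05/3 = .0167, .05/2 = .025 and .05, stopping at the first failure. The first step is the same, so the chance of at least one rejection must be the same. Any gain lies in the second and third rejections.

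**Power in hours.** Simulated trials with a shared routine-care arm, normal times with SD 13.03 h, and pairwise log-rank tests. The differences from routine care (massage/mirabilite/combination) are assumed.

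| Scenario | Each monotherapy, Bonferroni → Holm | All three, Bonferroni → Holm |
|---|---|---|
| 10/10/18 h, 18 per arm | .39 → .49 | .21 → .35 |
| 12/12/18 h, 18 per arm | .56 → .66 | .36 → .53 |
| 10/10/18 h, 14 per arm | .31 → .39 | .14 → .25 |

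In the first scenario the combination contrast goes from .90 to .91. Repeat runs differ by one or two hundredths.

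**Cross-check from f = 0.593.** Three normal z statistics with correlation 0.5 (shared control), 400,000 draws, mean z = d × √(n/2).
- Additive pattern (0, d, d, 2d): f = d/√2, so d = 0.593 × √2 = 0.839. At n = 14 the monotherapy mean z is 0.839 × √7 = 2.22. Against the two-sided .0167 critical value of 2.394, power is Φ(2.22 − 2.394) = .43. Holm gives .54. All three: .27 → .43. At n = 18: monotherapy .55 → .66; all three .38 → .56.
- Equal pattern (three active arms d better than control): f = d√3/4, so d = 0.593 × 4/√3 = 1.369. At n = 14: each contrast .89 → .94; all three .77 → .88. At n = 18: all three .90 → .96.

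**Error rates, one outcome, 14 per arm, same z-statistic simulation.**
- Global null: .044 under both rules.
- Only the combination effective (assumed hazard ratio 3): .031 Bonferroni, .040 Holm.
- One null arm beside assumed hazard ratios of 2 and 3: .016 and .031.
- Limiting case, two clearly effective arms and one null: the null contrast's rate goes from .0167 to as much as .05.

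**Two outcomes.** Six tests at .0167 have a bound of 6 × .0167 = .10. Holm run separately within each outcome leaves that bound at .10.

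**The case against.** A reader might infer that the rule is misnamed, called hierarchical while containing no hierarchy. The protocol does not support that. The exploratory contrasts are conditional on the primary ones, and that gate is the hierarchy. A flat Bonferroni threshold inside the first tier is consistent with it, so the word should stay.

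The rest of the opposing case is this. Bonferroni is valid, simple and correctly computed, so nothing is misstated. The effects in hours are assumed: the planning trial, as described, had three active arms and no routine-care arm, and the protocol does not say which outcome the 13.03 h belongs to. The simulated times are continuous, while flatus and defecation are assessed every 4 hours. The largest gain is on an all-three criterion that the Data Analysis section does not impose. Only the nominal bound is shared by the two rules. Finally, relaxing thresholds while two primary outcomes lack an alpha split adds to a looseness already there.

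Most of this stands, and it limits the point without removing it. The gain does not depend on one scenario: it has the same direction and a similar size under effects set in hours and under patterns calibrated to the protocol's own f. The hypothesis that all three strategies work makes the second and third rejections relevant, even without a formal all-three criterion. The two-outcome objection is a reason to define the family first, not a reason to keep the flat threshold.

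**Conclusion.** The flat .0167 is valid and is not an error. It is a less efficient choice than Holm at the same .05 familywise bound.

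In the scenarios tabulated above, each monotherapy contrast gains about 8 to 11 points in the hour-based and additive patterns, and about 5 points per contrast when all effects are equal at 14 per arm. The chance that all three are significant rises by about 6 to 18 points. The combination contrast gains about one point in the first scenario, and the chance of at least one significant contrast gains nothing.

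These sizes rest on assumed effects against routine care, normally distributed times, and every event observed. It would be too strong to say that Holm has the same error rate: it has the same bound, and its actual error is higher under partial nulls.

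**What to change.** Replace the fixed threshold with Holm over a stated family of primary contrasts:

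- three contrasts per outcome: ordered p-values against .05/3, .05/2, .05;
- one family across both primary outcomes: .05/6, .05/5, and so on to .05.

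State which family applies before choosing the thresholds. Only the six-test family, or a split of alpha between the outcomes, brings the overall bound to .05. Keep the two-tier gate and the word that describes it. If the gate needs all primary contrasts to be significant, which the text leaves open, Holm will also open it more often, so state the condition.

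The change needs no extra children, visits or data. It has three costs:

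- Actual error is somewhat higher under partial nulls, within the bound.
- Simultaneous intervals that match Holm are less simple. Unadjusted 95% CIs, which the Cox model already supplies, would be reported beside the adjusted p-values.
- A published threshold changes after 38 of 72 children had been randomised (January 2026). No interim analysis has been performed, so this remains credible if documented as an amendment before any unblinded analysis.
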